### 8.1.1 Other study parameters (if applicable)

- Date of birth
- Diagnosis + timing of diagnosis
- Number of acute hospitalizations in 6 months before consultation of palliative care team
- If inpatient clinic: hospitalization department
- Number of consults by palliative care team
- Number and type of specialists during MDO meeting where patient is discussed

## 8.2 Randomisation, blinding and treatment allocation

NA

## 8.3 Study procedures

As this is a retrospective data analyses study, informed consent will not be required.

The palliative care team hands over a list of new consults in the period between January and May 2016. The researcher appoints a research number to each subject on the list. With use of the electronic medical file and insight into DBC registration, the following variables will be collected:

| In 6 months before inclusion                        | Consultation: characteristics                                                                                                                                                                                                           | 6 months follow up                                                                                                                                                                 |
|-----------------------------------------------------|-----------------------------------------------------------------------------------------------------------------------------------------------------------------------------------------------------------------------------------------|------------------------------------------------------------------------------------------------------------------------------------------------------------------------------------|
| Acute hospitalizations
Disease/treatment history | 
 
- Date of birth
 
- Diagnosis
 
- Date of diagnosis
 
- Date of PT consultation
 
- Reason for PT consultation
 
- Number of consults by PT during
 
 | 
 
- Hospitalizations
 
- Emergency department visits
 
- Treatment (when wishes with regard to treatment were noted)
 
 |

|  |                                                                                                                                                                                                                                                                                                                                                                                                                                                    |                                                                          |
|--|----------------------------------------------------------------------------------------------------------------------------------------------------------------------------------------------------------------------------------------------------------------------------------------------------------------------------------------------------------------------------------------------------------------------------------------------------|--------------------------------------------------------------------------|
|  | hospitalization
- Wishes and expectations of the patient with regard to the palliative care team
- Agreements/wishes of patients noted with regard to hospitalization/ treatment / preferred place of dying
- Prognosis (estimated by nurse specialist)
- Contact between PT and GP/home care/care home: number of contacts, method, handover
For inpatient clinic:
- Hospitalization department
- Reason for hospitalization | - Date and place of death
- DBC financing: DBC registered & approved? |
|--|----------------------------------------------------------------------------------------------------------------------------------------------------------------------------------------------------------------------------------------------------------------------------------------------------------------------------------------------------------------------------------------------------------------------------------------------------|--------------------------------------------------------------------------|

#### 8.4 Withdrawal of individual subjects

NA

## 9. SAFETY REPORTING

NA

## 10. STATISTICAL ANALYSIS

Descriptive statistics (mean±SD, median (IQR) or count (%)) will be used to describe the study sample with regard to all outcomes.

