## **2. OBJECTIVES**

In this exploratory study, we will investigate opportunities and threats of a (transitional) palliative care team. Objectives:

- To explore reasons of hospitalizations of patients for whom a palliative team was consulted in the hospital;
- To explore why, when and by whom the palliative team was consulted;
- To explore needs and expectations of the patient with regard to the palliative care team;
- To investigate whether agreements with and wishes of patients (with regard to hospitalizations, treatments and preferred place of death) are fulfilled after they had a consultation from the palliative care team;
- To investigate prognoses estimated by nurse specialist with actual time to death;

- To explore communication between the palliative care team and GPs and home care/care homes;
- To explore which % of consultations is financed and what are reasons for not financing a consult (according to DBC- registrations)

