### 3. STUDY DESIGN

Retrospective analyses of patients with a palliative care team consultation between January and May 2016 in the OLVG location East.

We will analyze data on the period of the consultation itself, 6 months prior to first consultation (prior hospitalizations and disease history) and 6 months after first consultation (follow up).

*Timeline (recruitment of new consults of the palliative care team between January and May 2016)*

[figure not shown]

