#### **4.4 Sample size calculation**

Due to the exploratory nature of this study, a sample size calculation is not possible. In our opinion, a sample of 50-60 patients will be sufficient to explore the objectives of this study. With 175 complete consultations in 2015, inclusion of patients in the first 4 months of 2016 will result in a sample between 50-60 patients.

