#### **8.1 Study parameters/endpoints**

##### **Endpoints**

- Reasons for hospitalization of patients for whom a palliative team was consulted during hospitalization. With use of an expert panel, we will discuss preventability of these hospitalizations in the analysis phase of the study.
- Timing & reasons for palliative team consultation & profession of person who consulted the palliative care team
- Needs and expectations of patients with regard to palliative care team consultation

- Fulfilment of agreements with and wishes of patients (with regard to hospitalizations, treatments and preferred place of death)
  - o Agreements available/wishes noted during consults with palliative care team regarding future hospitalizations, treatments and preferred place of death
  - o Agreements and wishes fulfilled 6 months after consultation?
- Estimated prognosis by nurse specialist and actual time to death
- communication of the palliative care team with GPs and home care/carehomes:
  - o Timing & amount of communication
  - o Oral/written communication
  - o Content of handover
- Financing of consultations and reasons for not financing a consult (according to DBC-registrations)

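### Time to death is observed only to 6 months, yet Section 10 gives it ordinary descriptive summaries and specifies no per-patient comparison with the nurse's estimate

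*Protocol*

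**What the plan says.** Section 2 lists the objective "To investigate prognoses estimated by nurse specialist with actual time to death". Section 8.1 repeats it as a single endpoint, "Estimated prognosis by nurse specialist and actual time to death", without defining a difference, category match or other measure of agreement.

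Section 3 limits the period after consultation to "6 months after first consultation (follow up"). In the Section 8.3 table, "Prognosis (estimated by nurse specialist") is recorded at the consultation, and "Date and place of death" appears only in the 6-month follow-up column. The table has no field for the date a patient was last known alive, and the scale of the prognosis (a number or categories) is not given.

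Section 10 is one sentence covering every outcome: "Descriptive statistics (mean±SD, median (IQR) or count (%)) will be used to describe the study sample with regard to all outcomes".

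**The concern.** A patient alive at 6 months has no observed time to death. An ordinary mean needs a value for every patient, so survivors must be left out or entered as 6 months, and both choices pull the mean down. A median taken only over patients with a date of death is also too low. Section 10 neither warns against this nor says what to do instead.

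The error bears directly on the question asked. If survivors are dropped, patients who outlived their estimate by passing 6 months disappear, while patients who died early against a long estimate remain. The team could then be told that its nurses overestimate survival when they do not.

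The second difficulty would exist with no censoring at all. Section 10 describes the sample. A summary of estimates beside a summary of survival times does not show whether the estimate was right for each patient.

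**Working it through.** **The plan's own figure.** Section 4.4 states: "With 175 complete consultations in 2015, inclusion of patients in the first 4 months of 2016 will result in a sample between 50-60 patients". Check: 175 × 4/12 = 58.3, inside 50–60. It reproduces, and 58.3 is used below. There is no power calculation to check.

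**Assumption.** The documents give no 6-month mortality and no median survival; Section 11.2 says only that prognosis is poor. I assume exponential survival with true median *m* from 1 to 6 months, and a cut-off of 6 months.

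**Formulas.**
- True mean: θ = m / ln 2
- Share alive at 6 months: S = exp(−6 ln 2 / m)
- Mean among deaths: θ − 6S/(1 − S)
- Median among deaths: −θ ln[1 − 0.5(1 − S)]
- Mean with survivors entered as 6 months: θ(1 − S), which is too low by exactly the fraction S

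**Example, m = 3.** θ = 3/0.693 = 4.33. S = exp(−1.386) = 0.25. Deaths-only mean = 4.33 − 6 × 0.25/0.75 = 2.33 (46% low). Deaths-only median = −4.33 × ln(0.625) = 2.03 (32% low). Mean with survivors at 6 = 4.33 × 0.75 = 3.25 (25% low).

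| True median (months) | Alive at 6 months, of 58.3 | Deaths-only median | True mean | Deaths-only mean | Mean, survivors = 6 |
|---|---|---|---|---|---|
| 1 | 0.9 (1.6%) | 0.98 (2% low) | 1.44 | 1.35 (7% low) | 1.42 (2% low) |
| 2 | 7.3 (12.5%) | 1.66 (17% low) | 2.89 | 2.03 (30% low) | 2.52 (12.5% low) |
| 3 | 14.6 (25%) | 2.03 (32% low) | 4.33 | 2.33 (46% low) | 3.25 (25% low) |
| 6 | 29.2 (50%) | 2.49 (58% low) | 8.66 | 2.66 (69% low) | 4.33 (50% low) |

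**What retaining survivors does to the median.** If survivors are ranked as living beyond 6 months, the all-patient median is unbiased as long as more than half die in the window. In this model it is 1, 2 and 3 months in the first three rows, with no bias. The last row is the boundary, with exactly half dead. The IQR fails sooner: the exponential upper quartile is 2m, so it falls inside 6 months only when m ≤ 3.

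**Direction for nurse accuracy.** I simulated unbiased but imperfect nurses: log-scale SD of 0.8 between patients' prognoses and 0.7 for actual survival around each prognosis, both assumed. Among all patients, estimates are too long in 50%. Among deaths within 6 months only, they appear too long in 57%, 62% and 73% at medians of 2, 3 and 6 months. The size depends on the assumed spreads.

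**Separate summaries against paired comparison.** In a simulated sample of 58 with complete follow-up, perfect predictions and the same predictions randomly shuffled among patients gave identical summaries: median 3.44 months, IQR 1.39–6.12. Yet 100% of the perfect and 19% of the shuffled predictions lay within ±33% of actual survival, with correlations of 1.00 and −0.05.

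**The case against.** The strongest reply is that Section 10 does not force the bad analysis. It also lists counts with percentages, which is the form a table of correct, too long and too short would take. Both values are collected per patient and named together as one endpoint. A reader might infer that Section 10 allows only means and medians, or that individual accuracy cannot be measured. The documents support neither: the data permit pairing, and what is absent is any specification of it.

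It can also be said that the median is already listed and, with survivors retained, is unbiased when more than half die. That stands, so the deaths-only figures show one careless route and not an inevitable result. But Section 10 does not say to retain survivors, and the mean it equally allows is biased on either route.

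Two further limits stand. The apparent optimism needs imperfect estimates: if every estimate were exactly right, dropping survivors would leave paired differences at zero. And the true amount of censoring is unknown; at a median of 1 month it hardly matters.

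Finally, agreement measures are often left to an analysis plan. That would answer pure silence. Here the protocol does choose a method for all outcomes, and applied at face value to this endpoint it can mislead.

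**Conclusion.** The point holds at moderate severity. Section 10 assigns ordinary descriptive statistics to an outcome that the 6-month window censors, gives no rule for survivors, and specifies no within-patient comparison for an objective that needs one.

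The size rests on an assumed exponential model and an assumed range of medians. The bias is negligible at a true median of 1 month. By 3 months it is about a third for a deaths-only median and nearly half for a deaths-only mean. It is zero for the all-patient median when survivors are kept and more than half die. The lack of a paired measure does not depend on mortality.

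A reader might infer that this undermines the study as a whole. It does not. The Summary names reason for hospitalization as the main parameter; prognosis is the fifth of seven objectives in a descriptive study for which the protocol says "Due to the exploratory nature of this study, a sample size calculation is not possible".

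**What to change.** In Section 10, except this endpoint from the general rule and state:

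- Time to death is summarised by Kaplan-Meier from the date of the estimate, censored at 6 months after first consultation or at the date last known alive.
- Estimate and outcome are compared within each patient by cross-tabulating estimated against observed survival category, reporting the percentages correct, too long and too short with 95% confidence intervals.
- A 6-month survivor whose estimate lay wholly below 6 months counts as underestimated. A survivor whose estimate reached or exceeded 6 months is reported as not contradicted by 6 months, separately from correct, because a 7-month estimate for a patient who lives for years is not accurate.
- Where the file allows, vital status at data extraction is used to resolve the latter group. The study is retrospective, so this may already be on record.

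The categories should be fixed once the scale on which nurses recorded prognosis is known.

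Cost: a few sentences in Section 10, one extra field (date last known alive) and minor analysis work. The sample and the main parameter do not change.

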## 11. ETHICAL CONSIDERATIONS

### 11.1 Regulation statement

The study will be conducted according to the principles of the Declaration of Helsinki, the 7th revision (2013) and in accordance with the Medical Research Involving Human Subjects Act (WMO) and other guidelines, regulations and Acts

### 11.2 Recruitment and consent

The nurses of the palliative care team of the OLVG will hand over a list of patients consulted by the palliative care team between January and May 2016. Because of the retrospective design and poor prognosis of the patients, informed consent is not necessary and / or possible.

**11.3 Objection by minors or incapacitated subjects (if applicable)**

NA

**11.4 Benefits and risks assessment, group relatedness**

This study will give insight into the work of the palliative care team. A report with results will be send to the palliative care team and hospital directors in order to improve the work of the team.

**11.5 Compensation for injury**

NA

**11.6 Incentives (if applicable)**

NA

**12. ADMINISTRATIVE ASPECTS, MONITORING AND PUBLICATION**

**12.1 Handling and storage of data and documents**

Data will be handled confidentially and anonymously. Each recruited patient will get a research number. A secured subject identification code list will be used which is only accessible by the principle investigator.

**12.2 Monitoring and Quality Assurance**

NA

**12.3 Amendments**

Substantial amendments which would change the nature of the study will be notified to the METC that gave a favourable opinion.

Non-substantial amendments will not be notified to the accredited METC and the competent authority, but will be recorded and filed by the sponsor.

**12.4 Annual progress report**

The sponsor/investigator will submit a summary of the progress of the trial to the accredited METC once a year. Information will be provided on the date of inclusion of the first subject, numbers of subjects included and numbers of subjects that have completed the trial, serious adverse events/ serious adverse reactions, other problems, and amendments.

### **12.5 Temporary halt and (prematurely) end of study report**

Within one year after the end of the study, the investigator/sponsor will submit a final study report with the results of the study, including any publications/abstracts of the study, to the accredited METC.

## **13. STRUCTURED RISK ANALYSIS**

NA

